### 2.6. Databases

Participant-identifying data (names and surnames, clinical record numbers) will be pseudo-anonymized using a code to prevent access to personal information. Only the minimum necessary data will be collected for study purposes, including sex, age, other sociodemographic factors, diagnosis, and scores obtained from clinical scales. To maintain data security, the head of the Psychiatry Department at Hospital Universitario Fundación Jiménez Díaz and a collaborating researcher will be the only individuals with access to individual subject data. This access will be facilitated via a tool that associates participant codes with clinical record numbers through an external table separate from the web-based participant database. The web-based participant database is hosted on Amazon Web Services, with all communications encrypted via HTTPS protocol. It is protected by the following security measures:Firewall protection provided by the hosting provider, allowing access only to known services.IPTABLES-based firewall as an operating system firewall.Linux server with SNORT intrusion detection system.Integrity control of various operating system files with AIDE.Multiple rootkit detection systems (CHKROOTKIT and RKHUNTER).External audits conducted with METAEXPLOIT and NESSUS.

During database or equipment maintenance operations, access to the remote maintenance console will only be permitted from allowed IP addresses (firewall-level filtering). A summarized log of all maintenance work performed (who/when/why/actions taken) will be maintained, as will a log of all accesses to maintenance consoles (log files).

### 2.7. Data Management

The study’s sponsor and participating center, responsible for processing personal data, will be the Psychiatry Department of Hospital Universitario Fundación Jiménez Díaz. Data will not be made publicly available to preserve patients’ privacy, but authors can be contacted for collaboration proposals.

The lawful basis for data processing is the patient’s explicit consent, as demonstrated by the Informed Consent Forms. Data will be retained for the duration of the study and for a maximum period of 20 years thereafter to fulfil any legal obligations arising from the relationship. For data processed for scientific research purposes, the Control Authorities of the Autonomous Communities may, upon request by the data controller and in accordance with established regulatory procedures, agree to the full retention of certain data, considering their historical, statistical, or scientific value in accordance with applicable legislation.

Access to personal information will be restricted to the study physician and their collaborators, health authorities, the Research Ethics Committee, and the sponsor’s monitors and auditors. These individuals are bound by the duty of confidentiality inherent to their profession when necessary to verify study data and procedures, always maintaining confidentiality in accordance with current legislation, including:Regulation (EU) 2016/679 of the European Parliament and of the Council of 27 April 2016 on Data Protection (GDPR).Organic Law 3/2018, of 5 December, on Personal Data Protection and Guarantee of Digital Rights.Provisions related to patient autonomy, information rights, and clinical documentation as outlined in Law 41/2002, of 14 November.Any other applicable and current regulations.

Therefore, participants’ identities will not be disclosed to any person, nor will data be communicated to third parties, except in cases of medical emergency or legal requirement. Prior to the commencement of this study, a risk prevention analysis was conducted by an independent entity (Grupo Ático34 S.L.).

### 2.8. Statistical Analysis

Statistical analyses will be performed using R software version 4.5.3 and SPSS software version 30.0, or the latest versions available. All tests will be two-tailed, with 95% confidence intervals, and the level of statistical significance will be set at a *p*-value less than 0.05. The Morisky and Haynes scales (Morisky et al., 1986) will be measured prior to the intervention and again at the end of the sessions, and changes will be analyzed using Pearson’s correlation and simple regression. On the other hand, we will compare the total duration of antipsychotic exposure in the 6 months prior to the intervention with that in the 6 months following the intervention. Similarly, we will compare the average doses to which the sample was exposed before and after the intervention by calculating the recommended daily doses received.

To validate self-report questionnaires, sensitivity, specificity, positive predictive value, and negative predictive value will be calculated using medication collection data from the MUP as the gold standard. ROC curves will be constructed to determine the empirically optimal cut-off for classifying adherence, using the Youden index and reported with 95% confidence intervals, with PRE2DUP-derived antipsychotic exposure as the reference standard.

To explore factors associated with higher or lower adherence, a logistic regression will be conducted, with adherence as the dependent variable. Adherence will be operationalized using the PRE2DUP method (Tanskanen et al., 2015; Taipale et al., 2016), generating two continuous outcomes: total duration of antipsychotic exposure (days) and average daily dose in DDDs (Tanskanen et al., 2015). These continuous variables will be used as dependent variables in all regression analyses. Furthermore, linear correlations will be performed between adherence levels (using percentage of adherence as a continuous variable) and various potentially implicated factors. To identify factors independently associated with non-adherence, a multivariable logistic regression model will be constructed, incorporating sociodemographic and clinical variables as independent predictors and adjusting for potential confounders (age, sex, diagnosis, comorbidities, and urbanicity). Simple logistic regression and Pearson correlations will be conducted as preliminary exploratory analyses to inform variable selection for the multivariable model. Pre-post changes in adherence outcomes—including PRE2DUP-derived exposure duration and average daily dose in DDDs, as well as self-report scale scores—will be analyzed using linear mixed-effects models, with time (pre- vs. post-intervention) as a fixed effect and subject as a random effect, adjusting for diagnosis, age, and sex.

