### 1.5. Study Objectives

The objectives of our project are as follows:To validate self-reported digital adherence questionnaires using dispensing data from the MUP on antipsychotic medication as the gold standard.To identify factors associated with poor adherence by exploring correlations between various sociodemographic variables—available through the Patient Portal—and medication exposure as measured via the MUP.To evaluate the effectiveness of the intervention by reassessing patient adherence six months after the intervention.

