## 3. Ethics and Dissemination

### 3.1. Feasibility

The expected duration of participation for each subject is approximately 6 months. The overall duration of the project is estimated at 2 years. The extraction and data analysis method has been previously explored to guarantee feasibility.

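### Section 2.8 gives two unranked analyses for change in the self-report scales, one of which (Pearson correlation and simple regression) does not measure change, and their end-of-sessions reading does not match the six-month objective

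*Protocol article*

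**What the plan says.** All references are to the protocol article.

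- **Objective (Section 1.5).** The third objective is to "evaluate the effectiveness of the intervention by reassessing patient adherence six months after the intervention".
- **Outcomes (Section 2.5).** The main outcome is adherence measured by the Morisky-Green scale and the Haynes-Sackett question. The next sentence adds dispensing data (share of the previous six months exposed to antipsychotics) and ties that measure to the intervention's effectiveness.
- **First analysis of the scales (Section 2.8, opening).** The scales "will be measured prior to the intervention and again at the end of the sessions, and changes will be analyzed using Pearson’s correlation". Simple regression is named with it.
- **Dispensing (Section 2.8, next sentence).** Total exposure in the six months before the intervention is compared with that in the six months after it.
- **Second analysis of the scales (Section 2.8, close).** Pre-post changes in exposure duration, average dose and the self-report scores "will be analyzed using linear mixed-effects models, with time (pre- vs. post-intervention) as a fixed effect and subject as a random effect", adjusted for diagnosis, age and sex.
- **Limitations (Section 4.3).** The primary outcome is described as resting on dispensing data.
- **Participation (Section 3.1).** "The expected duration of participation for each subject is approximately 6 months".

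**The concern.** There are three linked problems.

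1. **Method.** Correlation and simple regression describe association. Applied to pre and post scores, they show whether people who scored high before also scored high after. They do not show whether the group improved. A significant result could be reported as a treatment effect when nothing had changed.
2. **Two analyses, no ranking.** The same scores receive a mixed model later in the same section. Since neither is marked as governing, exploratory or superseded, the choice could be made after the data are seen.
3. **Timing and outcome label.** If the Section 2.5 label stands, the main outcome has no stated reading at the horizon of objective 3. An end-of-sessions score reflects immediate response to a psychologist-led programme in which adherence is monitored. Section 1.2 itself warns that self-report is prone to recall and social-desirability bias.

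**Working it through.** **Inputs.** From Section 2.3: a one-sample means test with alpha 0.05, power 95%, d = 0.5, minimum n = 52, dropout up to 50%, target 110. From Section 2.8: two-tailed tests. The document gives no pre-post correlation of the scales, so values of 0, 0.5 and 0.8 are assumed.

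**Step 1: the plan's own figure.** By the normal approximation, n = ((1.960 + 1.645)/0.5)² = 51.98, so 52; with 50% dropout, 52/0.5 = 104. Both stated figures reproduce. The exact noncentral t gives 54 (power 0.950; at 52 it is 0.943), and 54/0.5 = 108 is still under 110. The sample size was therefore built for a test of mean change, not for a correlation, and it is not affected by this point.

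**Step 2: response to a mean shift.** Let X be the pre score and Y the post score, and add a constant c to every Y. Then cov(X, Y + c) = cov(X, Y) and var(Y + c) = var(Y). Hence r = cov/(SD_X·SD_Y) and slope = cov/var(X) do not change; only the intercept rises by c.

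**Step 3: when r becomes significant.** At n = 52, t(50) = 2.009, so critical r = 2.009/√(50 + 2.009²) = 2.009/7.351 = 0.273. A pre-post correlation above this gives p < 0.05 whatever the mean change.

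**Step 4: simulation.** n = 52, 20,000 replicates, share with p < 0.05. The true change is 0.5 SD of the differences, matching d = 0.5.

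| Assumed pre-post correlation | Pearson, no change | Pearson, true change | Paired test, no change | Paired test, true change |
|---|---|---|---|---|
| 0 | 5.1% | 5.1% | 4.9% | 93.9% |
| 0.5 | 97.3% | 97.1% | 5.1% | 94.3% |
| 0.8 | 100% | 100% | 5.1% | 94.2% |

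At each assumed correlation, the Pearson test rejects about equally often with and without improvement. The paired test holds its 5% level and has about 94% power. With two time points and complete data, the time effect in the mixed model amounts to this paired comparison.

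**Step 5: timing, side by side.**

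| Measure | Post-intervention reading stated | Status given |
|---|---|---|
| Self-report scales | End of sessions (2.8) | Main outcome (2.5) |
| Dispensing exposure | Six months after the intervention (2.8) | Effectiveness measure (2.5); primary (4.3) |

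The six-month objective is met by the second row and not by the first. Sections 2.5 and 4.3 disagree on which row is primary.

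**Step 6: participation.** If participation runs from the first of the ten sessions (Section 2.4) to six months after the last, it lasts the session period plus six months, which is more than six months. If it means active involvement only, with dispensing extracted from the database afterwards, about six months is possible. The text does not say which is meant.

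**The case against.** **A valid analysis is already there.** The mixed model at the end of Section 2.8 expressly covers the self-report scores and tests pre-post change, and the sample size is for a means test. This stands. A reader might infer that the plan has no proper test of change in self-report, and the document does not support that.

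**The six-month objective is already served.** Objective 3 speaks of adherence, not of self-report. The dispensing comparison covers six months on each side, Section 2.5 links it to effectiveness, and Section 4.3 calls it primary. This also stands. A reader might infer that the effectiveness objective goes unanswered, and it does not. What remains is the main-outcome label in Section 2.5.

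**The sentence does not say pre scores are correlated with post scores.** It might mean relating change scores to another variable, or regressing scores on time. The second would respond to a mean shift, and even a regression of post on pre moves its intercept. This stands in part. Steps 2 to 4 apply to r and the slope on the natural pre-versus-post reading, not to everything the wording could allow. Correlating change scores with another variable would not test mean change either. A regression on time that ignores the pairing would be a third analysis, still unreconciled with the mixed model.

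**Participation length.** Session frequency is not given in the text, the timeline figure is not available here, and the six months is approximate. A reader might infer that the follow-up cannot fit. That is not shown; only an ambiguity is.

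**Six-month self-report may not be worth having.** Given the protocol's own view of self-report bias and its estimate of about 30% Portal completion, making it the evaluated time point is debatable. This stands, so the fix offers it only as an option.

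**Conclusion.** The point holds as an internal inconsistency confined to the self-report outcome. Section 2.8 states one analysis of change that, read as pre against post, carries no information on mean change in r or the slope. It also states a second, sound analysis of the same scores and ranks neither. At n = 52 the first is significant once r exceeds 0.27; with no improvement that happens in about 97% of trials at an assumed pre-post correlation of 0.5, and in essentially all at 0.8. The invariance and the threshold are exact; the percentages depend on the assumed correlations.

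Separately, the end-of-sessions reading conflicts with objective 3 only while Section 2.5 keeps the scales as the main outcome, and Section 4.3 contradicts that label. Neither the sample size nor the six-month dispensing comparison is affected. The participation period needs clarifying and is not a demonstrated error.

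**What to change.** 1. In Section 2.8, delete Pearson's correlation and simple regression as the analysis of change in the scales, or label them exploratory. Make the mixed model at the end of that section the sole pre-post analysis. Cost: wording only.
2. Reconcile Sections 2.5 and 4.3 by naming six-month dispensing exposure as the primary effectiveness outcome and end-of-sessions self-report as a secondary, short-term outcome. Cost: wording only.
3. Optionally, send the scales again through the Portal six months after the last session. The cost is one more questionnaire and non-response. If the 30% completion estimate applied to 110 recruits, 0.30 × 110 = 33 would reply, fewer than 52. That estimate was made for the wider Portal population, so enrolled participants may respond differently.
4. In Section 3.1, state whether the participation period includes the six months after the sessions. Cost: one sentence.

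### Section 2.8 names logistic regression for adherence but fixes continuous outcomes for every regression, so the logistic models of objective 2 cannot be run as written

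*Protocol article*

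**What the plan says.** The relevant text is one paragraph of Section 2.8 of the protocol article. In order, it says:

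- The model for higher or lower adherence: "a logistic regression will be conducted, with adherence as the dependent variable".
- Adherence is operationalised by the PRE2DUP method, "generating two continuous outcomes: total duration of antipsychotic exposure (days) and average daily dose in DDDs".
- The rule on outcomes: "These continuous variables will be used as dependent variables in all regression analyses".
- Linear correlations are also planned, "using percentage of adherence as a continuous variable".
- The adjusted analysis: "To identify factors independently associated with non-adherence, a multivariable logistic regression model will be constructed", with age, sex, diagnosis, comorbidities and urbanicity as adjustment variables.
- The preliminary step: "Simple logistic regression and Pearson correlations will be conducted as preliminary exploratory analyses to inform variable selection for the multivariable model".

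The paragraph ends with linear mixed-effects models for the pre-post comparison.

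The preceding paragraph of Section 2.8, on the questionnaires, states that "sensitivity, specificity, positive predictive value, and negative predictive value will be calculated using medication collection data from the MUP as the gold standard". It also plans ROC curves with a Youden cut-off, taking PRE2DUP exposure as the reference standard. Section 1.5 words objective 2 as exploring correlations between sociodemographic variables and medication exposure measured in the MUP.

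**The concern.** The type of model and the type of outcome are both fixed, and they do not match. An analyst has to drop one of the two instructions, and the text does not say which.

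The choice matters. Under the rule on outcomes there are two adjusted models, one for days and one for DDDs, with effects expressed as differences in days or in dose. Under the logistic instruction there is one adjusted model, with odds ratios for a binary non-adherence class that the paragraph never defines. These answer different questions and may point to different factors. Section 1.6 predicts that statistically significant risk factors will be found, so the outcome and model behind that statement should be settled before the data are seen.

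**Working it through.** **The plan's own figure.** The article gives no sample size, power or event count for the objective 2 regressions. The 52 and 104 in Section 2.3 belong to the pre-post test and do not bear on this point. The check is therefore one of consistency.

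**Step 1. The instructions side by side (all Section 2.8).**

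| Element | What is fixed |
|---|---|
| First-named model | Logistic |
| Preliminary models | Simple logistic, plus Pearson correlations |
| Adjusted model | Multivariable logistic |
| Outcome of every regression | Exposure days and average DDDs, both continuous |
| Outcome of the linear correlations | Percentage of adherence, continuous |

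The first three rows conflict with the fourth. The last row conflicts with nothing.

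**Step 2. Why a logistic model cannot take these outcomes.** The contribution of one patient to the log-likelihood is y·log(p) + (1 − y)·log(1 − p), where p is the fitted probability. This has a sensible maximum only for y between 0 and 1. Take y = 182 days, full exposure if six months are counted as 182 days (an assumption). The term becomes 182·log(p) − 181·log(1 − p), which grows without limit as p approaches 1. The same happens for any average dose above 1 DDD.

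**Step 3. Trial fit.** Outcomes were simulated for 1640 patients under assumed distributions: days as 182 times a Beta(2.2, 0.9) variable with a small shift by one covariate, truncated to 0–182, and DDDs as Gamma with shape 3 and scale 0.4. A standard logit fit was refused for both outcomes because the values lie outside the unit interval.

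**Step 4. Does another section resolve it?**

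- The Youden cut-off is chosen in the questionnaire validation, against PRE2DUP exposure as reference. That analysis needs the reference already split into two classes, so it cannot supply the split.
- Section 2.4 refers to patients with adherence problems without a numerical definition.
- Days divided by the length of the window would lie between 0 and 1 and could enter a fractional logit. The article does not state that model, and it would not serve for DDDs.

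**Step 5. What a binary outcome would depend on.** In the same simulated data, cut-offs of 50%, 60%, 70% and 90% of the window classed 21%, 32%, 44% and 75% of patients as non-adherent. The odds ratio for the covariate stayed between 0.84 and 0.90. These are illustrative figures, not trial data. The size of the class depends heavily on the cut-off. In this one simulation the odds ratio depended on it much less.

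**The case against.** The strongest reply is that objective 2 is exploratory and survives. Section 1.5 speaks of correlations, and correlations on continuous adherence are planned and feasible. This stands. A reader might infer that the whole of objective 2 cannot be run, and the article does not support that. What the correlations lack is adjustment: the multivariable logistic model is the only analysis of independently associated factors, and it is among those that fail.

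Three further readings are tempting and go too far.

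- **That the article wrongly omits a MUP threshold for the validation and for selecting intervention patients, or will choose one after seeing the data.** A condensed article may leave an operational threshold to the full protocol, and nothing here says it will be chosen late. The contradiction is different in kind: two stated rules exclude each other, and a later document could not honour both.
- **That predictors will be screened on significance, making the final p-values too optimistic.** The article says only that preliminary analyses inform selection. It gives no p-value rule, and the named adjustment variables already cover most of the factors listed in Section 2.5.
- **That an ample number of events per predictor measures the problem.** Such a count presupposes the binary outcome that is in doubt.

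It is also fair to say that the pre-post effectiveness analysis is unaffected, since its mixed models use continuous outcomes.

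**Conclusion.** The contradiction is real, sits within one paragraph of Section 2.8, and is not resolved elsewhere in the article. All the logistic models of objective 2, simple and multivariable, cannot be run as written. The correlations can. There is no numerical error to size: the extent is the whole logistic component, and with it the only confounder-adjusted analysis of factors associated with non-adherence. The conclusion rests on the wording and on the form of the logistic likelihood. The simulated figures only illustrate it. The text should be corrected before data extraction. Section 2.4 expects a start in September 2026.

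**What to change.** Choose one of two routes and state it in Section 2.8.

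1. **Keep the continuous outcomes (preferred, because they are the ones declared).** Replace the simple and multivariable logistic regressions with continuous-outcome regression: for example, linear regression with robust standard errors for exposure days and for DDDs, or a fractional logit for percentage of time exposed. Enter the listed sociodemographic and clinical factors together, which makes the preliminary selection step unnecessary, and report effect sizes with 95% confidence intervals.
2. **Keep logistic regression.** Delete the sentence that makes the continuous variables the outcome of all regressions. Use a binary MUP definition of non-adherence set by the sponsor before extraction, and use the same definition as the binary reference for sensitivity, specificity and the ROC curves.

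No cut-off is proposed here. How patients are identified for the intervention is for the sponsor to reconcile with whatever definition is adopted.

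The cost is analysis wording only, with no new data.

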## 2. Materials and Methods

### 2.1. Setting and Design

This project will be carried out in the Psychiatry Departments of four hospitals in the Community of Madrid associated with the Instituto de Investigación Sanitaria Fundación Jiménez Díaz: Hospital Universitario Fundación Jiménez Díaz, Hospital Rey Juan Carlos, Hospital General de Villalba, and Hospital Infanta Elena. This protocol combines three complementary methodological perspectives: (1) a validation study; (2) an observational study; and (3) a single-arm pre-post study to evaluate the intervention. All patients identified with poor adherence will receive the same psychoeducational program; the pre-intervention measurement will serve as a comparator.

Figure 1 shows the outline of the project.

This protocol describes a study with three design perspectives to achieve our objectives:Validation study to explore the accuracy of digital self-report questionnaires.Observational study for identifying factors associated with non-adherence.Pre-post study to assess the effectiveness of the intervention

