### 2.3. Sample Size Calculation

According to our preliminary data, there are 5458 patients in our hospitals diagnosed with schizophrenia or bipolar disorder and with active antipsychotic dispensing registered in the MUP. Of these, an estimated 90% are registered on the Patient Portal, yielding an initial estimated sample of 4900 people.

Considering that completion of self-administered questionnaires on the Patient Portal is estimated to be around 30%, we expect an approximate sample of 1640 patients to perform the validation calculations for the adherence scales.

The sample size was calculated using G*Power (v3.1) for a one-sample means test (alpha = 0.05, power = 95%, effect size d = 0.5), yielding a minimum of 52 participants. This was based on previous studies exploring the ability of educational interventions to improve medication adherence in the medium term (Loots et al., 2021). Accounting for an anticipated dropout rate of up to 50%, the adjusted minimum is 104. We therefore set a recruitment target of 110 participants, well within the estimated pool of 656 patients expected to present with poor adherence.

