### 2.4. Procedure and Intervention

Project is expected to start in September 2026. We will access the MUP database and cross-reference it with data from the Patient Portal to identify our target sample, that is, those patients who received antipsychotic dispensations who also appear as active users of the Patient Portal. Within the entire sample, we will identify factors associated with adherence issues in the six months prior to the study. The entire sample will then be invited via a message through the Patient Portal to complete the self-report adherence questionnaires.

Finally, the subset of the sample identified with adherence problems will be the target sample for the intervention. Adherence problems to antipsychotics in people with schizophrenia or bipolar disorder are around 40–50%, although the variability in the studies is considerably high (Lingam & Scott, 2002). From the identified pool of patients with poor adherence, a recruitment target of 110 participants has been established. This sample size was determined using G*Power (v3.1) for a one-sample means test (alpha = 0.05, power = 95%, effect size d = 0.5), which requires a minimum of 52 participants (Loots et al., 2021). The final target of 110 accounts for an anticipated dropout rate of up to 50%, ensuring sufficient statistical power despite the high attrition typically observed in this clinical population.

The intervention program will be designed by clinical psychologists with experience in treating patients with bipolar disorder and schizophrenia after a review of the best protocols available in the literature. Presumably, participants will receive psychoeducational materials on the importance of adherence and the potential for mishap management. Tablet handling tips and medication-taking schedules will be reviewed. Participants will also be invited to a telehealth intervention comprising 10 online group psychotherapy sessions delivered via videoconference. These sessions will include cognitive-behavioral measures to manage adherence problems, and adherence will be monitored. Psychotherapy sessions will be led by clinical psychologists, and two sessions will feature testimonials from stabilized patients (See Figure 2).

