### 2.5. Outcomes

The study’s main outcome is treatment adherence, which was measured through the Morisky-Green 7-item scale (Morisky et al., 1986) and the Haynes-Sackett question (Sackett & Snow, 1979). Additionally, MUP will be used to calculate the percentage of time patients were exposed to antipsychotic treatment over the previous six months, measuring the effectiveness of the intervention. We will also use the MUP to record prescriptions for other medications, including those for general medical conditions.

This study will also gather sociodemographic and clinical data available through the Patient Portal, including sex, age, date of birth, urbanicity, and the presence of physical comorbidities.

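### The multivariable model for factors linked to non-adherence pools four hospitals without adjusting for hospital, so a hospital difference can appear as a patient-factor association, urbanicity above all

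*Protocol article*

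**What the plan says.** Section 2.1 states that the project is "carried out in the Psychiatry Departments of four hospitals in the Community of Madrid". Section 2.4 sets the population for the factor analysis: "Within the entire sample, we will identify factors associated with adherence issues in the six months prior to the study". Section 2.3 puts its size at about 4900 ("yielding an initial estimated sample of 4900 people").

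Section 2.8 describes a multivariable logistic model for factors independently associated with non-adherence, "incorporating sociodemographic and clinical variables as independent predictors" and "adjusting for potential confounders (age, sex, diagnosis, comorbidities, and urbanicity". Candidates are screened first: "Simple logistic regression and Pearson correlations will be conducted as preliminary exploratory analyses to inform variable selection for the multivariable model".

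The covariates in section 2.5 are listed as "including sex, age, date of birth, urbanicity, and the presence of physical comorbidities". Hospital is not named there, nor among the minimum data items in section 2.6. The pre-post mixed model in 2.8 has subject as a random effect and adjusts for diagnosis, age and sex.

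**The concern.** The second objective is to find factors associated with poor adherence, and the abstract and conclusions say that these will inform targeted interventions. A model that claims independent association should account for the most obvious grouping in the data, which is the hospital. The article writes out an adjustment set and hospital is not in it.

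Bias arises when two things occur together: adherence differs between hospitals after the listed adjustments, and a studied factor is unevenly distributed over hospitals. Urbanicity is the most exposed of the named factors because it is a property of place and may follow hospital. If it does, a difference between services could be reported as a patient risk factor, and an intervention could be aimed at the wrong target. At a sample size of about 4900, fairly small imbalances can reach significance.

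**Working it through.** **Inputs from the article.** Four hospitals (2.1); factor analysis in the entire sample (2.4); 5458 × 0.90 = 4912, rounded in 2.3 to 4900; adherence problems in 40–50% (2.4); two-sided 0.05 (2.8). I use 40%, which also matches the pool of 656 in 2.3 (656 / 1640 = 0.40). No figure stated in the article depends on the adjustment set. The 52, 104 and 110 belong to the pre-post part and do not change.

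**Inputs assumed.** Poor adherence by hospital and urban share by hospital. The article gives neither, so both are varied. The hospital difference should be read as what remains after adjustment for age, sex, diagnosis and comorbidities.

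**Two-group calculation.** Collapse the hospitals into two equal groups with poor adherence *a* and *b*. Let half the patients (2450) be urban and assume no urbanicity effect within either group. A share *s* of urban patients attends the first group, and the same share of non-urban patients attends the second.

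- Urban: p₁ = s·a + (1 − s)·b
- Non-urban: p₂ = (1 − s)·a + s·b
- OR (non-urban vs urban) = [p₂/(1 − p₂)] / [p₁/(1 − p₁)]
- z = (p₂ − p₁) / √(2 × 0.40 × 0.60 / 2450) = (p₂ − p₁) / 0.0140

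| a, b | s | p₁ | p₂ | OR | z |
|---|---|---|---|---|---|
| 35%, 45% | 0.9 | 0.36 | 0.44 | 1.40 | 5.7 |
| 35%, 45% | 0.7 | 0.38 | 0.42 | 1.18 | 2.9 |
| 37.5%, 42.5% | 0.7 | 0.39 | 0.41 | 1.09 | 1.4 |

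For example, in the first row (0.44/0.56)/(0.36/0.64) = 1.40 and 0.08/0.0140 = 5.7. If a = b or s = 0.5, then p₁ = p₂ and the bias is zero.

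**Four-hospital simulation.** Four equal hospitals, 4900 patients, poor adherence centred on 40%, true urbanicity OR of 1, 300 replicates per scenario. Logistic models were fitted without and with three hospital indicators. Hospital log-odds are spaced so that the outer two lie 1.34 SD either side of logit(0.40) = −0.405. An SD of 0.1, 0.2 or 0.3 therefore means a spread of about 37–43%, 34–47% or 31–50%. The hospital with the largest urban share is given the lowest poor adherence, which is the least favourable alignment. ORs are urban versus non-urban, so they fall below 1.

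| Urban share by hospital | SD | OR without | False positives without | OR with | False positives with |
|---|---|---|---|---|---|
| 95/70/50/20% | 0.1 | 0.89 | 52% | 1.00 | 6% |
| 95/70/50/20% | 0.2 | 0.79 | 98% | 1.00 | 7% |
| 95/70/50/20% | 0.3 | 0.71 | 100% | 0.99 | 4% |
| 60/55/50/45% | 0.1 | 0.98 | 6% | 1.00 | 4% |
| 60/55/50/45% | 0.2 | 0.96 | 12% | 1.00 | 5% |
| 60/55/50/45% | 0.3 | 0.94 | 19% | 1.00 | 4% |

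With no hospital difference, or the same urban share everywhere, the model without hospital gives an OR of about 1.00 and a false-positive rate of 4–7%. Simulation error at 5% is √(0.05 × 0.95 / 300), about 1.3 percentage points.

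**The case against.** **The list may be open.** Section 2.8 admits sociodemographic and clinical predictors in general, the list in 2.5 is illustrative, and a condensed article may leave centre terms to a fuller document. This carries some weight: nothing forbids adding hospital. But the confounders are written out by name, hospital is neither a sociodemographic nor a clinical variable, and the screening step does not bring it in.

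**The premises are not documented.** A reader might infer that each hospital serves a distinct area, that urbanicity follows hospital, and that prescribing or follow-up differs between sites. The article states none of these. All four hospitals belong to one research institute in one region and use one prescription module. This stands, and it makes the point conditional.

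**Hospital may be a mediator.** A reader might call hospital a direct confounder. If residence determines hospital, hospital lies downstream of urbanicity, and adjusting for it can remove part of a real association. Both calculations assume that the hospital difference is unrelated to urbanicity itself. This stands too. It is a reason to report both estimates, not to leave hospital out altogether.

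**Small imbalances do little.** A reader might infer that any modest hospital difference would make urbanicity highly significant. The figures do not support that: the mildest two-group case has z = 1.4, and a mild urban mix gives false-positive rates of 6–19%. Large distortion needs strong separation of urbanicity by hospital, which is where the two effects are hardest to disentangle.

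**The outcome may not be binary.** Section 2.8 also says that continuous exposure measures are the dependent variables in all regressions. The odds ratios above would not carry over to days or doses, but the mechanism would.

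**Conclusion.** The point holds in conditional form. The factor model in 2.8 names an adjustment set for a four-hospital sample and leaves out hospital, so a hospital difference can appear as a patient-factor association, most plausibly for urbanicity. Its size cannot be fixed from the article. Under the assumptions shown, with about 4900 patients and no true urbanicity effect, the spurious odds ratio ranges from 1.09 (z = 1.4) to 1.40 (z = 5.7), and it vanishes if either imbalance is absent.

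It would be wrong to conclude that the urbanicity result will be spurious, or that the pre-post comparison is affected in the same way: there, each patient is compared with himself or herself and the subject effect absorbs stable hospital differences. This is a desirable improvement to an exploratory objective, not a threat to the study.

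**What to change.** Add hospital to the recorded data items, and state in section 2.8 that the cross-sectional multivariable factor models include hospital as a fixed effect with three indicator terms. Four hospitals are too few to rely on a random effect or cluster-robust standard errors. The pre-post mixed model needs no change on this account.

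Report the urbanicity estimate with and without hospital, and tabulate urbanicity by hospital. If the two nearly coincide, say that they cannot be separated and do not report urbanicity as an independent risk factor.

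The cost is one data field, a line or two of wording and three degrees of freedom out of about 4900 patients. The real downside is a wider interval for urbanicity where it overlaps with hospital. Section 2.4 expects a start in September 2026, so the change should be made before data extraction.
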